### Interrupted Time Series

ITS using segmented regression has several strengths over the pre-post study design. It controls for secular trends over time, provides powerful, easy to understand visual outputs, and may improve generalisability to the wider population
^7,
8,
19^. For this study, data are available to evaluate both policies described above in an ITS analysis.

The two interventions in this study were introduced at specific, well defined time points, allowing for clear separation of pre- and post-intervention periods.
Figure 1 provides a timeline for the interventions in questions and
Table 3 provides details of the planned analyses and time periods included in each. As shown in
Figure 1, the same 12-month time period is used for both ITS analyses meaning they are not independent. However, there is insufficient time or data points to prevent this overlap, and this will be discussed as a potential limitation of the study.

**Table 3. T3:** Planned ITS analyses.

Policy change	Dates	Analyses
Change in TXA dose policy	Pre-intervention 01/11/2008 – 31/07/2011 Excluded implementation (lag) period 01/08/2011 – 31/01/2012 Post-intervention * 01/02/2012 – 31/01/2013	PRIMARY – Population-level effects of TXA policy for all patients undergoing THR or TKR
Introduction of preoperative anaemia screening programme	Pre-intervention * 01/02/2012 – 31/01/2013 Excluded implementation (lag) period 01/02/2013 – 31/07/2013 Post-intervention 01/08/2013 – 31/07/2014 (sensitivity analysis 01/08/2013 – 28/02/2019)	PRIMARY – Population-level effects of anaemia screening programme for ***all patients*** undergoing THR or TKR (with equal number of data points pre- and post-intervention)
		SECONDARY - Effect on anaemic subpopulation ***eligible for any*** ***treatment*** as per anaemia pathway (Hb <120g/L, female or 130g/L, male) **, modelled against non-anaemic cohort
		SECONDARY - Effect on anaemic subpopulation ***eligible for iron*** treatment only (Hb 105–119g/L female, 115–129g/L male & ferritin 12- 100), modelled against non-anaemic cohort (excluding those with Hb <105 or <115 and those referred to GP/haematologist).
		SECONDARY - Effect on anaemic subpopulation ***given iron*** treatment only (as above but only those given iron), modelled against non-anaemic cohort (same exclusion as above) – per protocol analysis

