* Post-intervention period for TXA policy is the same as the pre-intervention period for anaemia screening programme analysis. **includes GP referral, haematology referral or any form of iron

An early step in ITS analysis is to generate summary statistics for each time period and undertake simple pre-post comparisons
^20^. This will be performed in this study and later compared to the results from ITS and RDD analyses.

***Data description.*** ITS is said to work best with short-term outcomes that change quickly after implementation of an intervention or after a clearly defined lag period
^8^. This study is examining short-term outcomes; however, some delays to observed changes in outcomes after policy implementation are expected. The orthopaedic department has previously reported that a 6-month lag period was required to fully adopt the increased TXA dose policy
^16^. This same lag will therefore be incorporated into this ITS analysis. Regarding the introduction of the preoperative anaemia screening programme, staff running the anaemia service report that this started promptly on 01/02/2013, after detailed planning, and uptake was rapid. However, a lag to observed changes in outcomes will be inevitable due to surgical waiting list times. Comparing screening and surgery dates for the first 10 anaemic and 10 non-anaemic patients from the cohort shows all but one had their surgery within 6 months of screening. Therefore, a 6-month implementation (lag) period is also considered appropriate following introduction of the anaemia screening service (
Figure 1). Lag periods will be accounted for by excluding this data from the primary analysis
^21^. As individual procedure-level data are available, including data indicating whether or not anaemia screening was received, an alternative approach to handling the lag period for the analysis of the anaemia screening programme, could be to model the intervention as a continuous implementation variable ranging from 0 to 1, instead of as a binary (0/1) variable. This would allow the effect of the intervention to be modelled as a weighted average during the 6-month implementation period, which could be a more efficient use of the data available. A sensitivity analysis of this alternative method for handling the 6-month implementation period will be included in this study.

ITS requires sequential measures of the outcome, at regular intervals, before and after the intervention time points
^20,

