As individual-level data are available, including data on the treatment received as part of the anaemia screening programme, there are several ways the ‘anaemic’ subgroup can be defined and analysed to give different information. These will be explored as secondary analyses. The primary analysis will include all patients undergoing THR/TKR in the time period, with no splitting into anaemic or non-anaemic subgroups, to assess the impact of introducing the anaemia screening programme on the entire population of patients undergoing THR or TKR. Previous pre-post studies, on an earlier version of this dataset, suggest the effect size is large enough for this to show through even though only a subpopulation of patients receive treatment for anaemia. Secondary analyses such as splitting the data into those defined as being anaemic (by the anaemia pathway being used) or non-anaemic, allow for modelling with a control group and evaluation of the effects of the screening programme on the subpopulation expected to receive some treatment, (i.e. iron, GP or haematology referral), and hence benefit from introduction of the anaemia pathway. It may also be possible to explore, specifically, the effects of iron treatment on the subpopulation of anaemic patients eligible (ITT) or actually given (PP) iron as part of the anaemia screening programme.
Table 3 details the planned ITS analyses and, where appropriate, how the data will be split into two cohorts for secondary analyses. 

It is expected that the total number of procedures performed each month will be close to, or greater than, 100 for each time point in the primary analyses. However, as the data is split into cohorts (i.e. anaemic v non-anaemic), the number of procedures per month will reduce. This will likely increase the variability in the outcomes over time if reported as proportions (i.e. transfusion rate). Sensitivity analyses using event counts not rates will be conducted where the number of procedures per month drops below 30.

Time varying confounders specific to the primary outcome of this study may include other PBM interventions; those relevant will be discussed in turn. A restrictive blood transfusion policy was introduced Trust-wide in 2007 and has been unchanged since
^16,

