**Figure 2. f2:**
[figure not shown]
Northumbria Healthcare NHS Foundation Trust anaemia pathway demonstrating haemoglobin threshold values used to determine treatment
^17^.

Treatment options from the pathway (
Figure 2) include iron (oral or IV) or referral for further investigation (to GP or haematologist) prior to surgery. This means it may be possible to examine the effects of the anaemia screening policy for all anaemic patients (including all treatments), but also to isolate the effects of treatment with iron by excluding patients who do not qualify for iron treatment (as per the pathway in
Figure 2). Data permitting these variations will be explored. 

***Addressing threats to validity.*** Manipulation of treatment status by patients through manipulation of the assignment variable (Hb concentration) is highly unlikely. However, it is possible the reporting of the assignment variable could be manipulated by clinicians, although there is a protocol which healthcare professionals are required to, and report they, strictly adhere to. Nonetheless, steps will be taken to assess the internal validity of the data. A plot of assignment variable (Hb) against probability of receiving treatment will be created to inform if a sharp or fuzzy design is most appropriate
^29^. A histogram of the assignment variable (Hb) data will be visually inspected for bunching around the threshold values. This will also be tested using the McCrary density test
^32^. To test if groups either side of the threshold are comparable, summary statistics of non-outcome variables will be presented for those who fall just either side of the threshold. Formal testing (such as t-test for continuous variables) will be undertaken to assess for any statistically significant differences between groups either side of the threshold. It is predicated that some non-outcome variables such as age or comorbidities may affect outcome. As such sensitivity analyses incorporating these as covariates are planned regardless of the comparability of the two groups. If no differences between groups either side of the threshold are seen, this supports the assumption that assignment around the threshold is random and supports that there has been no manipulation of treatment status, similar to a RCT

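### The given-iron interrupted time series has no pre-intervention series, and the related iron-only exclusions can change case mix at the interruption or at the Hb cut-off

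*SAP article*

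**What the plan says.** Table 3 (Interrupted Time Series) sets the anaemia pre-period as "Pre-intervention * 01/02/2012 – 31/01/2013", excludes February to July 2013 as lag, and runs the post-period from 01/08/2013 to 31/07/2014. On the programme itself, the Data description paragraph reports that "this started promptly on 01/02/2013".

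Two of the secondary anaemia analyses in Table 3 concern iron:

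- The third takes patients with "Hb 105–119g/L female, 115–129g/L male & ferritin 12- 100" and models them against a non-anaemic cohort, with the exclusion worded as "excluding those with Hb <105 or <115 and those referred to GP/haematologist".
- The fourth, labelled per protocol, is "as above but only those given iron), modelled against non-anaemic cohort (same exclusion as above".

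The text under Addressing threats to validity describes the two sets as the "subpopulation of anaemic patients eligible (ITT) or actually given (PP) iron as part of the anaemia screening programme".

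The RDD uses data from the start of the programme. The opening of the Regression discontinuity section assumes that patients just above and just below the threshold (Hb 120 g/L female, 130 g/L male) come from one population. After Figure 2 the plan says it may be possible to "isolate the effects of treatment with iron by excluding patients who do not qualify for iron treatment", data permitting. The pathway's treatments are iron and referral to a GP or haematologist.

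**The concern.** An ITS needs the same kind of patient in the series before and after the interruption. An RDD needs the same kind of patient on both sides of the cut-off. Receipt of programme iron and referral through the pathway are consequences of the intervention, so selecting on them can act on only one side of the comparison.

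If it does, the composition of the anaemic series changes at the very point where the effect is estimated. The non-anaemic control removes changes common to both series. It cannot remove a change in who makes up the anaemic series alone. At stake are the analyses meant to say whether iron, as distinct from the whole programme, reduced transfusion.

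**Working it through.** **1. The plan's own count.** February 2012 to January 2013 is 12 months, and August 2013 to July 2014 is 12 months. Both agree with the 12 points per segment that the plan intends. The plan gives no sample size or power for the iron-only analyses.

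**2. Who can be in the given-iron series.** Membership requires being "actually given (PP) iron as part of the anaemia screening programme". The programme began on 01/02/2013 and the pre-period ends on 31/01/2013. Read literally, 0 of the 12 pre-intervention months contain a member, against the minimum of 8 that the plan calls desirable. No pre-segment can be fitted. The article names no substitute group for the pre-period.

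**3. If the pre-period is filled with a wider group.** Let *p* be the risk in patients who would pass the post-period filter, *s* the share of the wider group who would pass it, and *RR* the risk in those filtered out relative to *p*. With no treatment effect:

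- pre-period risk = *s·p* + (1 − *s*)·*RR·p*
- post-period risk = *p*
- spurious change = −(1 − *s*)(*RR* − 1)·*p*

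None of these inputs is in the plan. Assuming *p* = 10%, the change in percentage points is:

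| *s* | RR 1.0 | RR 1.2 | RR 1.5 | RR 2.0 | RR 3.0 |
|---|---|---|---|---|---|
| 0.4 | 0 | −1.2 | −3.0 | −6.0 | −12.0 |
| 0.6 | 0 | −0.8 | −2.0 | −4.0 | −8.0 |
| 0.8 | 0 | −0.4 | −1.0 | −2.0 | −4.0 |

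For example, at *s* = 0.6 and RR 1.5: −(0.4)(0.5)(10) = −2.0 points, from 12% to 10%. The sign reverses if the filtered-out patients have lower risk: at RR 0.5 the same formula gives −(0.4)(−0.5)(10) = +2.0 points.

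**4. ITS simulation with no treatment effect.** Assumptions: 12 + 12 months, 25 anaemic patients per month before filtering, 125 controls per month at 3% risk, *s* = 0.6, a level-change model with control, no autocorrelation term, 1000 runs. Excluded-patient risks of 10, 15, 20 and 30% gave mean estimates of about 0, −2.1, −4.0 and −7.9 points, with p ≤ 0.05 in 6, 12, 29 and 70% of runs. With one definition in both periods the mean estimate was about 0, with rejection in 6–7%.

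**5. Referral.** The Table 3 footnote and the text after Figure 2 list referral among the pathway's treatments. A filter on pathway referral can therefore remove nobody before 01/02/2013, whichever series it is applied to. The part of the exclusion based on Hb can be applied identically in both periods and is harmless.

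**6. RDD.** Nobody above the threshold qualifies for iron. Removing every non-qualifier would leave no comparison group, so the exclusion must be confined to patients below the cut-off unless a laboratory criterion such as ferritin is applied to both sides. A simulation of one-sided exclusion with no treatment effect (assumed N = 6000, *s* = 0.6, logistic model, 400 runs), with excluded-versus-eligible odds ratios of 1, 1.5, 2 and 3, gave threshold odds ratios of 0.98, 0.83, 0.73 and 0.57. Rejection was 3, 8, 17 and 50%. Without the exclusion the odds ratio was 0.99–1.01, with rejection in 4–5%.

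**The case against.** Most of the case on the other side limits the point rather than removing it.

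- *Ferritin.* A reader might infer that ferritin exists only after the programme began, or only below the threshold. The article does not say so. It gives Hb as the illustration of a screening result, a condensed article need not list every variable, and Figure 2 is not shown. If ferritin was measured comparably in both periods, the Hb and ferritin part of the third analysis can be applied consistently. This stands.
- *Referral.* In Table 3 the exclusion follows the mention of the non-anaemic cohort, so it is unclear whether it trims the anaemic series, the control or both. This also stands, which is why the point is limited to any series to which it is applied.
- *RDD.* The plan only says the iron variation may be possible, and does not say that patients above the cut-off are kept whatever their ferritin. It already considers a fuzzy design and plans comparisons of non-outcome variables either side, with covariate adjustment. These checks may reveal a one-sided exclusion but do not cure it.
- *Importance.* The iron analyses are secondary, and partly hedged. No primary conclusion rests on them.

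None of this supplies pre-period members for the given-iron series. That gap follows from the plan's own dates and definition.

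**Conclusion.** The point holds in a limited form. For the given-iron ITS the defect is structural: it has no pre-intervention series, and any substitute is a differently selected group. For the referral exclusion and the RDD exclusion, the comparison breaks wherever the filter works on one side only.

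A reader might go further and conclude that a spurious benefit is bound to appear. The plan does not support that. Taken literally, the given-iron ITS yields no estimate at all. Otherwise the size and direction depend on how the excluded patients' risk differs, and the bias in the proportion is zero if the risks are equal. The 2-point drop is an illustration resting on an assumed 10% risk, 60% eligible and a 1.5-fold risk in those excluded.

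Nor does the point reach the primary all-patient ITS or the any-treatment cohort, which is defined by Hb alone. Severity: should-fix.

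**What to change.** **ITS.** Define the iron-range cohort in both periods by the plan's own Hb bands alone (105–119 g/L female, 115–129 g/L male). Add the ferritin criterion only if ferritin is shown to be measured comparably in both periods. Make no exclusion on referral or iron receipt. Drop the given-iron ITS, or label it a description of treated patients with no pre-post contrast.

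**RDD.** Keep all patients near the cut-off, apply a ferritin restriction only if ferritin is measured on both sides, and use the fuzzy design already contemplated for iron receipt.

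**Interpretation.** A Wald or fuzzy estimate divides the change in outcome by the change in iron uptake. The programme and the threshold also trigger referral, so any effect of referral would be credited to iron. Report the estimate as a pathway effect, or as an iron effect only under the stated assumption that referral has no effect of its own.

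**Cost.** Revised wording and, if a scaled estimate is wanted, a two-stage model in R. The Hb-band effect is diluted by patients who did not receive iron, and any iron-specific estimate will have wider intervals.

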## Statistical Analysis Plan

### Data source

Over time the orthopaedic department at Northumbria Healthcare NHS Foundation Trust (NHCT) has introduced a range of interventions aimed at improving post-operative outcomes for patients undergoing elective lower limb arthroplasty. These changes have been well documented in a series of published pre-post cohort studies (
Table 1)
^14,
16,
17^. This study will focus on the impact of two policy changes: 1) increased dose of TXA; and 2) introduction of preoperative anaemia screening. This study will not assess the impact of introducing an enhanced recovery programme (as the data are not available); however, this is included in
Table 1 as it represents the time when the initial TXA policy (15mg/kg) was introduced (the pre-intervention period for the TXA analysis).

**Table 1. T1:** Summary of previously published pre-post comparative cohort studies of interventions introduced in NHCT aimed at improving arthroplasty patient outcomes.

Author, year	Intervention	Pre-intervention	Post-intervention	Statistically significant outcomes reported by authors (p<0.05)
**Malviya, 2011** ^14^	Multimodal Enhanced Recovery Programme *	Jan 2004 – April 2008 (n=1500)	May 2008 – Nov 2009 (n=3000)	Reduced mortality, transfusions and LoS
**Morrison, 2017** ^16^	Increased dose of IV Tranexamic acid (30mg/kg max 2.5g)	May 2008 – July 2011 (n=2637)	Feb 2012 ** – Jan 2013 (n=1814)	Reduced transfusions
**Pujol-Nicholas,** **2017** ^17^	Introduction of pre-operative anaemia screening and optimisation pathway ***	Feb 2012 – Jan 2013 (n=1814)	Feb 2013 – May 2014 (n=1622)	Reduced transfusion, readmissions, critical care admissions, LoS and costs.

* Includes introduction of IV Tranexamic acid, 15mg/kg [max 1.2g], at induction of anaesthesia ** Policy introduced in August 2011. This study allowed a 6-month implementation period to ensure the change in practice had been adopted *** The impact of these policies are being assessed further in this study, with an updated dataset LoS = length of hospital stay

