### Outcomes

The primary outcome is the proportion of procedures requiring perioperative allogenic RBC transfusion (within 7 days of surgery). Secondary outcomes are the quantity of blood transfused per procedure (RBC units), LoS per procedure (in days), critical care admission rate per 100 procedure (within 30 days post-surgery) and emergency readmission rate per 100 procedures (within 30 days post-surgery)
^1,
2,
17^.

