21^. In keeping with many ITS studies, individual-level outcome data will be converted to, and presented as, proportions or means at monthly intervals and a segmented-regression analysis performed
^21^. ITS plots will be generated and visually inspected to determine if linear or non-linear regression modelling is appropriate. A minimum of 8 data points pre- and post-intervention are desirable
^20,
21^. It is expected the shortest time frame being analysed in this study will include 12 months/data points, thus surpassing this requirement. The power of an ITS analysis is increased if there are an equal number of data points pre- and post-intervention
^22^. In the case of preoperative anaemia screening there are expected to be 12 data points in the pre-intervention period but 60 in the post-intervention period. As such, to increase power of this analysis this period will be cut to include only 12 time points, after the 6 month lag period, for the primary analysis of the anaemia screening policy. Sensitivity analysis including all post-implementation data points will be conducted.

***Addressing threats to validity.*** Time varying confounders are the main threat to the validity of ITS studies
^21^. These are specific to each ITS study and are carefully considered later in this SAP. However, the most robust way to account for time varying confounders, even those that are unknown, is to model against a control group. This could either be a different population not exposed to the intervention or, if individual-level data are available, by splitting the data into two groups, one group targeted by an intervention and another that is not. In this study, data for a different group of patients is not available for either intervention. The TXA policy is targeted at all THR or TKR patients so this data cannot be split. However, the anaemia screening policy targets a specific subgroup of anaemic patients with treatments so the population can be split into two groups to increase the robustness of this analysis. As such the two interventions will be modelled separately: 1) the TXA intervention without a control group, and 2) the anaemia screening intervention with a control group.

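### The sensitivity analysis for small split cohorts uses event counts with no stated denominator, so it mixes procedure volume with transfusion risk

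*SAP article*

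**What the plan says.** Under Outcomes, the SAP article defines the primary outcome with a denominator: "The primary outcome is the proportion of procedures requiring perioperative allogenic RBC transfusion (within 7 days of surgery". Under Interrupted Time Series, Data description, the main analyses keep it: "individual-level outcome data will be converted to, and presented as, proportions or means at monthly intervals and a segmented-regression analysis performed".

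Under Addressing threats to validity, the plan expects ample numbers in the all-patient series: "total number of procedures performed each month will be close to, or greater than, 100 for each time point in the primary analyses". It then recognises that the secondary analyses will be thinner: "as the data is split into cohorts (i.e. anaemic v non-anaemic), the number of procedures per month will reduce". Because proportions from small months are variable, it adds: "Sensitivity analyses using event counts not rates will be conducted where the number of procedures per month drops below 30".

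No offset, exposure term or other adjustment for volume is given for the count analyses, and their regression scale is not stated. Table 3 says that the anaemic cohorts are modelled against a non-anaemic cohort.

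**The concern.** The plan is right that proportions from small months are noisy. The stated remedy changes the quantity being estimated. A proportion says how likely a transfusion was, and a bare count says how many occurred. If fewer anaemic patients are operated on in one period, the count falls even when each patient's risk is unchanged.

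The analysis is there to test whether the small-cohort results are robust. If it responds to volume, agreement with the proportion-based result may be spurious and so may disagreement. A fall in volume after the anaemia pathway began would push the count in the direction of benefit.

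**Working it through.** **1. Inputs.** From Table 1: "Feb 2012 – Jan 2013 (n=1814", which is 12 months, and "Feb 2013 – May 2014 (n=1622", which is 16 months. From Data source: 20,772 procedures from January 2008 to March 2019, which is 135 months. The document gives neither the anaemic share nor the transfusion risk, so both are assumed below.

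**2. Monthly volume implied by Table 1.** Volume = n / months.
- Before the anaemia pathway: 1814/12 = 151.2 a month.
- After it: 1622/16 = 101.4 a month.
- Ratio: 101.4/151.2 = 0.67, a difference of −32.9%. The raw cohort sizes differ by only 10.6% because the periods differ in length.

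Both figures agree with the plan's expectation of about 100 or more a month.

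**3. Effect on a bare count.** Expected events = volume × share × risk. With share and risk constant, the ratio of expected counts equals the ratio of volumes, 0.67. The ratio of risks is 1.

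**4. What the control group does.** Assume a 15% anaemic share, 20% risk in anaemic patients and 5% in the others, all constant, with the volumes of step 2.
- Anaemic: 151.2 × 0.15 × 0.20 = 4.54 events a month before and 101.4 × 0.15 × 0.20 = 3.04 after; change −1.49 (unrounded inputs).
- Non-anaemic: 151.2 × 0.85 × 0.05 = 6.42 before and 101.4 × 0.85 × 0.05 = 4.31 after; change −2.12.
- Log scale: 0.67/0.67 = 1, so the shared change cancels.
- Linear count scale: −1.49 − (−2.12) = +0.62 events a month, a spurious excess.

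With 3% risk in the non-anaemic group instead, its counts are 3.85 and 2.59 (change −1.27), and the linear contrast is −1.49 − (−1.27) = −0.22, a spurious reduction. On a linear scale the error can go either way.

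**5. Simulation without a control group.** There were 600 series per setting, with 12 + 12 months and the six-month gap, constant risk, Table 1 volumes, assumed anaemic share 10–19% and risk 5–20%, analysed by Poisson regression at two-sided 0.05. In the segmented model, the level term was significant in 5–12% of series without an offset and in 2–5% with log(procedures) as offset. The median level ratio, taken from a level-only fit, was 0.65–0.68 without the offset and 0.99–1.04 with it.

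**6. The trigger.** At Table 1 volumes a cohort has fewer than 30 procedures a month if its share is below 30/151.2 = 19.8% before the change and below 30/101.4 = 29.6% after it. A cohort with a share between these meets the rule only after the change. The plan does not say what happens then, or whether the larger control cohort is also converted to counts.

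**7. Reliability of Table 1.** It reports 3000 procedures for May 2008–November 2009 (19 months, 157.9 a month) but 2637 for May 2008–July 2011 (39 months, 67.6 a month), although the second period contains the first. The dataset averages 20,772/135 = 153.9 a month. The 1622 cohort includes the excluded lag months and stops in May 2014, before the planned window closes in July 2014.

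**The case against.** The strongest reply is that little depends on this rule. It adds sensitivity analyses to the proportion-based ones and replaces none of them. It operates only below 30 procedures a month, which the all-patient series is not expected to approach. The split cohorts have a non-anaemic control, and step 4 shows that a shared proportional change in volume cancels on a log scale. One might add that a statistician would supply an offset in any case.

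The limits on scope stand. The rest stands only in part. A model with an offset is a rate model, and the text asks for counts in place of rates. The scale is not fixed, and on a linear scale the control does not in general cancel a shared change. Nor need the change be shared: the pathway refers some anaemic patients to a GP or haematologist before surgery, and one cohort is defined by iron actually given, so cohort size may respond to the programme itself.

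A reader might infer from Table 1 that volume really fell by a third across the anaemia change. Step 7 shows why it cannot carry that: its cohorts come from earlier publications and its own figures do not behave as total volumes. For the same reason, the 67.6 a month before the tranexamic acid (TXA) change neither shows a volume shift there nor contradicts the expectation that "It is expected that the total number of procedures performed each month will be close to, or greater than, 100".

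**Conclusion.** The concern holds in a limited form. Followed as written, the small-cohort count analysis cannot separate procedure volume from transfusion risk, and so is not a sound check on the secondary anaemic-cohort results. Bias arises if cohort volume differs between periods and the control does not remove the difference. Its size is unknown from the document. The ratio of 0.67 illustrates the mechanism under Table 1 volumes, constant risk and no effective control.

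Three stronger readings are not supported. The primary all-patient results are not undermined, because the count rule does not reach them. A false reduction is not certain: it depends on volume, control and scale, and the simulated error rates are modest in the segmented model and come from a setting without the planned control. The document also does not show that the main monthly-proportion models are unweighted or would give a counterfactual below zero, because it states neither weights nor baseline rates.

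Severity: should-fix.

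**What to change.** Replace the count-only sentence with a segmented model that keeps the denominator. Possible wording:

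> Where a split cohort has few procedures per month, a sensitivity analysis will model monthly events out of monthly procedures by segmented binomial or quasi-binomial regression, or by Poisson or negative binomial regression with log(procedures) as offset. It will use the same control group and the same handling of autocorrelation as the corresponding secondary analysis. Monthly procedure numbers will be reported by cohort.

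If the threshold of 30 is kept, state whether one month below it is enough, and that both cohorts and both periods change model together.

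The cost is SAP wording. Procedure-level data, and so the denominators, are already held, the analysis is still pending according to Study status, and no data are lost.

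### The small-cohort sensitivity analysis of the time series models event counts without a denominator, so it mixes surgical volume and case share with transfusion risk

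*SAP article*

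**What the plan says.** The Outcomes section sets the scale: "The primary outcome is the proportion of procedures requiring perioperative allogenic RBC transfusion (within 7 days of surgery". The Interrupted Time Series section keeps to it for the main models: "individual-level outcome data will be converted to, and presented as, proportions or means at monthly intervals and a segmented-regression analysis performed".

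Under Addressing threats to validity, the article notes that splitting the data into cohorts leaves fewer procedures a month, and gives the consequence: "This will likely increase the variability in the outcomes over time if reported as proportions (i.e. transfusion rate". Its remedy is "Sensitivity analyses using event counts not rates will be conducted where the number of procedures per month drops below 30".

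No offset, binomial likelihood, weighting or other denominator is mentioned for these counts. The planned checks on changes in the population cover demographics such as age and sex, and ischaemic heart disease. Monthly surgical volume and the anaemic share are not among them. Table 3 models the split anaemia cohorts against a non-anaemic cohort. The post-intervention period is given as "Post-intervention 01/08/2013 – 31/07/2014 (sensitivity analysis 01/08/2013 – 28/02/2019").

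**The concern.** The check is meant to show whether results in the anaemic and iron-eligible cohorts, and in any small strata, survive thin monthly denominators. Changing from a rate to a bare count changes the quantity estimated. A fall in throughput, or in the proportion of patients classed as anaemic, would look like fewer transfusions. A rise would look like harm. The check could then appear to support or contradict the rate-based result for reasons unrelated to transfusion risk, and the plan has no step that would reveal this.

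**Working it through.** **1. The plan's own volume figure.** The article expects about 100 or more procedures a month in the primary analyses. Dividing cohort sizes by inclusive calendar months:

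- Before screening, "Feb 2012 – Jan 2013 (n=1814"): 1814/12 = 151.2 a month.
- After screening, "Feb 2013 – May 2014 (n=1622"): 1622/16 = 101.4 a month.
- Whole dataset, January 2008 to March 2019: 20,772/135 = 153.9 a month.

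All three agree with the expectation. The tranexamic acid pre-cohort, "May 2008 – July 2011 (n=2637"), does not: 2637/39 = 67.6.

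**2. Where the rule would apply.** At 151.2 a month, a cohort falls below 30 if its share is under 30/151.2 = 19.8%. At 101.4 a month the limit is 30/101.4 = 29.6%. The SAP article gives no anaemic share. Shares of 15% to 20% are assumed below.

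**3. What a count measures.** Expected events = N × s × p, with N monthly procedures, s the cohort's share and p the risk. The log of the count is log N + log s + log p. Only p is the outcome. Without a denominator, any step or trend in N or s adds to the level and slope terms.

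**4. Noise.** Assume s = 15%, p = 20% and procedure numbers that vary as Poisson. Expected events are 151.2 × 0.15 × 0.20 = 4.53 a month.

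- Relative standard deviation of the count: 1/√4.53 = 0.47.
- Relative standard deviation of the proportion at its expected denominator: √(0.80/4.53) = 0.42.

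The count is no steadier than the proportion it replaces.

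**5. Illustration, anaemic series alone.** Take the Table 1 ratio 101.4/151.2 = 0.671 with constant risk. Expected events go from 4.53 to 3.04 a month. In 600 simulated series per setting (12 + 12 months, 6-month gap, segmented Poisson; share 15% with risk 20%, or share 19% with risk 30%, all assumed):

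| Segmented model | Median level-change ratio | p < 0.05 |
|---|---|---|
| Count, no offset | 0.64 to 0.68 | 14% to 18% |
| log(procedures) offset | 0.99 to 1.01 | 2% to 4% |

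With stable volume (share 15%, risk 20%), the ratios are 0.96 and 0.99, and neither model shows a material bias.

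**6. With the non-anaemic control.**

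- *Log scale, stable share:* both series fall by 0.671, and 0.671/0.671 = 1. The volume change cancels.
- *Linear count scale, stable share:* volume falls by 151.17 − 101.38 = 49.79 a month. The anaemic series changes by −0.15 × 0.20 × 49.79 = −1.49 events. The control changes by −0.85 × 0.02 × 49.79 = −0.85 at an assumed control risk of 2%, or −0.85 × 0.05 × 49.79 = −2.12 at 5%. The spurious contrast is −1.49 + 0.85 = −0.64 or −1.49 + 2.12 = +0.63 events a month, so its sign depends on the risks.
- *Log scale, share shifts, volume and risks constant:* from 15% to 20% gives (20/15)/(80/85) = 1.42. From 20% to 15% gives (15/20)/(85/80) = 0.71.

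**7. Can Table 1 be read as volume?** It lists 3000 procedures for May 2008 to November 2009 (19 months), but 2637 for May 2008 to July 2011 (39 months), which contains that period. If 2637, 1814 and 1622 were complete volumes, the remaining 20,772 − 2637 − 1814 − 1622 = 14,699 procedures would fall in 135 − 39 − 12 − 16 = 68 months, or 216 a month. The 16-month post-screening cohort also includes the six lag months that the time series excludes, and ends two months before the planned 12-month window does.

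**The case against.** The strongest reply is that Table 3 does not plan an anaemic series alone. With a non-anaemic control, constant risk and the full one-third fall, simulations under assumed shares of 15–20%, anaemic risks of 8–30% and control risks of 2–5% flagged the differential level change in 4–6% of runs on a log scale and 5–7% on a linear count scale. That is close to nominal. This stands for the controlled short-window contrast when the anaemic share is stable. It does not cover a shift in share, or strata by surgery type or sex run without a control. A flag rate near 5% also does not make the point estimate unbiased, as the linear-scale arithmetic shows.

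Three stronger readings are tempting, and the document does not support them:

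- *Volume fell by a third when screening began.* The arithmetic is right, but these are sizes of earlier published cohorts that contradict each other as volumes. Projections of volume to 2019 from the same figures are no firmer.
- *False findings in half or more of analyses.* Step-only count models without a control gave 49–73% in the step 5 settings, but the plan is for segmented regression, and for a control in the split cohorts.
- *The anaemic cohort on counts and its control on rates.* The rule can be read that way, but rerunning the whole contrast on counts is at least as natural.

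It is also fair that the rate analyses are retained, and that a condensed article might leave an offset unstated. The wording, however, sets counts against rates, and a count model with a log-procedures offset is a model of rates.

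**Conclusion.** The point holds as a defect in a stated sensitivity analysis. Read literally, the rule no longer estimates the proportion defined as the outcome, does not solve the small-number problem that prompted it, and is sound only if monthly volume and anaemic share are both stable. Neither is checked.

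The size cannot be fixed from the document. If volume is stable and shares hold, the bias is immaterial. If volume changed by the Table 1 ratio, an uncontrolled count series would show a level ratio near 0.67 at constant risk. A controlled log-scale contrast would show none with a stable share, but a five-point move in share between 15% and 20% would shift it to 1.42 or 0.71. These figures rest on assumed shares and risks. The primary all-patient time series is not affected; the exposure is confined to the small secondary cohorts and strata.

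**What to change.** Replace the count rule with one of these for event outcomes in cohorts below 30 procedures a month:

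- a segmented binomial (logistic) model of events out of procedures; or
- a segmented Poisson or quasi-Poisson model of counts with log(monthly procedures) as offset.

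State that the same model is used for the anaemic and non-anaemic cohorts, and report monthly procedure numbers for each cohort so that changes in volume and share can be seen.

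The cost is one sentence in the plan and one model option in R. The denominators are already in the procedure-level dataset, and the article says analysis is still pending, so the change can be made prospectively.
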